**Fig. 2 Fig2:**
[figure not shown]
Schematization of the randomization processes

### Design description

The study will be conducted in five interventions (Intervention 1 (I1); Intervention 2 (I2); Intervention 3 (I3); Intervention 4 (I4); Intervention 5 (I5)), and the groups will be randomized to perform these interventions at several moments, with a 1-week interval between interventions. Data collection will always be performed at the same period of day and in air-conditioned environments.

### Procedures

#### Study interventions

The description of the interventions is as follows:*Intervention 1 (I1)*: the HRV behavior of the participant will be evaluated without exposure to any recovery technique or any type of stress. The follow-up period will be 2 h*Intervention 2 (I2)*: the HRV behavior of the participant will be evaluated before the application of the massage technique. Evaluations will be performed 2 h after massage application*Intervention 3 (I3)*: the HRV behavior of the participant will be evaluated before the implementation of the stress protocol. The autonomic modulation of heart rate will be evaluated 2 h after the end of the stress protocol*Intervention 4 (I4)*: the HRV behavior of the participant will be evaluated before the stress protocol, followed immediately by the massage technique, as well as 2 h after the completion of the massage in order to observe if HRV is anticipated*Intervention 5 (I5)*: the HRV behavior of the participant will be evaluated before the stress protocol, and the massage technique will be applied at the exact moment of ANS recovery, determined by the study of Almeida et al. [11] who used the same stress protocol, and posteriorly there will be follow up for 2 h in order to see if there is potentiation of HRV recovery

The first three interventions of the study (I1, I2, and I3) will be performed to establish the basal behavior of the study variables and/or before the two different stimuli (massage and stress), and for possible explanations and discussion of the study.

In Interventions 4 and 5, analysis of the effects of massage on post-exercise recovery, and the comparison of the effects of massage when performed immediately after stress or 1 h after stress, will be performed.

It is emphasized that at I5 the massage will be applied 60 min after the end of the stress protocol, as this was the exact time identified in the study by Almeida et al. [11] for the recovery of the internal control functions of the body after the same stress protocol as used in the present study.

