### Procedure details

#### Stress protocol

Participants will be submitted to a stress protocol consisting of a jumping program and a maximum short-term cycling test [11]. The jumping program consists of 10 sets of 10 jumps with a 1-min interval between sets. During the jump, participants will be instructed to place their hands on their hips and during the jump landing to flex their knees at 90° in order to avoid compensations. After the jump, the participants will have 1 min of rest and then perform the Wingate anaerobic test protocol, which will be performed on a cycle ergometer Biotec 2100 (Cefise, Nova Odessa, Brazil). The test consists of a 5-min warm-up and the test itself. During warm-up the participant will pedal at a speed of 60 to 90 rpm with a fixed load of 1.0 kg, and in the second and fourth minutes the participant will be required to perform a sprint, reaching the maximum possible speed according to individual perception. After the 5-min warm-up the anaerobic test will be performed, consisting of maximum pedaling for 30 s with a stipulated load of 0.075 kp·kg^-1^ of the participant’s body mass. During the sprints and test, verbal stimuli will be provided to stimulate maximum performance.

This stress protocol was chosen due to the study of Almeida et al. [11] which investigated the protocol and concluded that it is effective in triggering derangements in the ANS. Immediately after completion of the protocol, participants will be directed to a stretcher, where they will lie down to perform the massage immediately after stress (I4) or 1 h after stress (I5), or to remain at rest (I1, I2, and I3), and then be followed up for 2 h to capture the RR intervals.

It is worth mentioning that after the stress protocol all participants will be required to drink 180 ml of water in order to standardize hydration and avoid the influence of blood volume on the results of the present clinical trial.

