#### Massage protocol

According to a recent systematic review with meta-analysis [19], the effects of massage seem to be better when it is applied for between 5 and 12 min. Thus, the massage in the present protocol will have a total of 12 min duration, being 6 min on the anterior region of the thigh (3 min for each limb) and 6 min on the posterior region of the trunk. The choice of these anatomical sites was due to the effort required by the stress protocol and location of the preganglionic neurons of the ANS, respectively.

For massage on the anterior thigh (quadriceps femoris muscle) the participant will be placed in the dorsal decubitus and the massage initiated on the dominant limb and then the non-dominant limb, and posteriorly, in the ventral decubitus position, massage will be performed on the trunk (paravertebral muscles). The techniques of surface and deep slip will be used, the latter being presented at two intensities, moderate or intense, being gradually increased. The massage will be performed towards the muscle fibers, from distal to proximal and following the lymphatic flow.

The massage will be performed by three physiotherapists specializing in sports physiotherapy, previously trained by a sports physiotherapist with 10 years’ experience in sports massage.

A pilot study will be conducted for the training of the physiotherapists who will apply the massage in a standardized manner regarding the intensity, rhythm, form of application of massage, and application dynamics through data collection. The physiotherapists will be required to present excellent correlations between them in order to be eligible to perform the technique.

The massage will have the rhythm: 1 s of slip and 1 s for return of the hand to the initial position, totaling 2 s of slip (Table 1). The rhythm of the massage will be controlled by an electronic metronome that will only be used by the therapists during performance of the technique.

**Table 1 Tab1:** Massage protocol for the anterior thigh region and posterior trunk region

Anatomical site	Slip	Pressure	Rhythm	Time (seconds)	Total slips per technique
Anterior thigh	Surface	Light	1 slip every 2 s	60	30
	Deep 1	Moderate	1 slip every 2 s	60	30
	Deep 2	Intense	1 slip every 2 s	60	30
Posterior trunk	Surface	Light	1 slip every 2 s	120	60
	Deep 1	Moderate	1 slip every 2 s	120	60
	Deep 2	Intense	1 slip every 2 s	120	60

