#### Primary outcome

HRV will be used as the primary outcome as it is an important overall marker of post-exercise recovery [16]. The HRV analysis will be performed from the series of RR intervals captured by the cardiofrequency meter Polar Electro Oy – model V800, and linear methods analyzed in the time domain and frequency domain, and Poincaré plot. All HRV indices will be obtained through the *software* Kubios HRV – version 2.0 [20].

For this analysis, the time series of RR intervals will initially be subjected to digital filtering using the *software* Kubios HRV – version 2.0, supplemented by manual filtering, to eliminate premature ectopic beats and artifacts, and only series with more than 95% of sinus beats will be included in the study [20]. Through visual analysis of the time series, the absence of ectopic artifacts or beats that can interfere in the HRV analysis will be observed.

During the recovery period, the evaluated moments will be: R1 (initial 5 min of rest before performing the interventions), R2 (initial 5 min of recovery), R3 (fifth to 10th minutes of recovery), R4 (10th to 15th minutes of recovery), R5 (20th to 25th minutes of recovery), R6 (30th to 35th minutes of recovery), R7 (40th to 45th minutes of recovery), R8 (50th to 55th minutes of recovery), R9 (60th to 65th minutes of recovery), R10 (70th to 75th minutes of recovery), R11 (90th to 95th minutes of recovery), and R12 (115th to 120th minutes of recovery). It is worth mentioning that 256 consecutive RR intervals will be obtained at these moments [21].

HRV indices in the time domain (rMSSD and SDNN), frequency domain (low-frequency spectral component (LF) and high-frequency spectral component (HF)), and the Poincaré plot (SD1 and SD2) will be evaluated [22].

In the time domain, the rMSSD Index corresponds to the square root of the square mean of the differences between the adjacent normal RR intervals in a time interval expressed in milliseconds and evaluates the behavior of the parasympathetic autonomic modulation [22], while the SDNN Index represents the standard deviation of all normal RR intervals recorded in a time interval, expressed in milliseconds, and is considered a measure of global variability, that is, it evaluates both sympathetic and parasympathetic modulation [22].

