#### Secondary outcomes

The study will include five measures of secondary outcomes: individual touch perception, which will be collected at baseline of the first randomized intervention, and blood pressure, heart rate, respiratory rate, and oxygen saturation, which will always be collected at baseline and during the 2 h of recovery at minutes 1, 3, 5, 7, 10, 20, 30, 40, 50, 60, 70, 80, 90, 100, 110, and 120. In addition, in I5 these variables will be collected 1 h prior to the application of the massage at minutes 1, 3, 5, 7, 10, 20, 30, 40, 50, and 60.► *Blood Pressure*○ Blood pressure will be verified by an indirect method using a stethoscope (Littmann, Saint Paul, MN, USA) and an aneroid sphygmomanometer (Welch Allyn – Tycos, Skaneateles Falls, NY, USA) fixed on the left arm of the volunteers. To avoid errors in determining blood pressure, these measurements will be performed by a single evaluator. The measurements will be performed according to the criteria established by the VII Brazilian Hypertension Guidelines [25]► *Heart rate*○ To verify the heart rate, a cardio frequency meter (Polar Electro Oy, Kempele, Finland – model V800) will be used [22]► *Respiratory rate*○ Respiratory rate measurements will be performed by counting the respiratory incursions for 1 min without the participant being aware of the process, so that the usual breathing characteristics are not modified [26]► *Oxygen saturation*○ Oxygen saturation will be verified by means of a pulse oximeter (Mindray PM-50 Pulse Oximeter, China). The pulse oximeter is a device that provides blood saturation readings by evaluating the absorption behavior of oxyhemoglobin and deoxyhemoglobin in relation to red and infrared light lengths [27]► *Questionnaire on individual touch perception*○ The *Touch Avoidance Questionnaire* [28] is a questionnaire composed of 37 questions that evaluate the experience of the touch received by another person. One question addresses how invasive the touch is from the unknown person and the other question addresses the touch experience by a professional whose profession requires the same touches, such as masseurs. The questionnaire contains 37 questions, and the questions offer the alternatives: “true” and “false” for scoring the touch experience; however, we will only use two adapted questions and the answers will be given on a linear scale equivalent to 10 cm, where 0 is without any discomfort and 10 is extremely uncomfortable

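### Recovery moments R2–R12 start 0, 12 and 72 minutes after exercise in I3, I4 and I5, so same-label comparisons mix massage with natural recovery, mainly in the early and middle windows

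*Protocol article*

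**What the plan says.** In the Protocol article, Study interventions, the follow-up is anchored differently by session.

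- I3 (stress only): "The autonomic modulation of heart rate will be evaluated 2 h after the end of the stress protocol".
- I4 (stress, then massage): "as well as 2 h after the completion of the massage in order to observe if HRV is anticipated".
- I5 (stress, one hour, massage): after the massage, "posteriorly there will be follow up for 2 h in order to see if there is potentiation of HRV recovery". The same section adds that "at I5 the massage will be applied 60 min after the end of the stress protocol".

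The Stress protocol section gives the same order. Participants receive massage or rest, "and then be followed up for 2 h to capture the RR intervals". Under Massage protocol, "the massage in the present protocol will have a total of 12 min duration".

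The Primary outcome section lists one set of moments for every intervention, beginning "R2 (initial 5 min of recovery), R3 (fifth to 10th minutes of recovery" and ending with R12 at 115–120 min. It does not say which event is minute zero. The Secondary outcomes section treats the hour before massage in I5 as additional to the 2 h of recovery: "In addition, in I5 these variables will be collected 1 h prior to the application of the massage at minutes", followed by a list of times up to minute 60.

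The Statistical analysis section compares the HRV indices and cardiorespiratory parameters between I1–I5 and between rest (R1) and R2–R12. It uses ANCOVA adjusted for the baseline value of the variable. Time since exercise is not mentioned.

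**The concern.** The Background asks whether immediate massage brings autonomic recovery forward and whether massage after recovery enhances it. The contrasts that answer this are I4 with I3, I5 with I3, and I5 with I4. If the same R label means a different time since exercise in each session, part of any difference is recovery that would have happened without massage. Provided HRV recovers steadily after exercise, that part favours massage over no massage and later massage over earlier massage. Adjusting for a pre-stress baseline cannot remove it, because the baseline carries no information on elapsed time. A massage with no effect could be reported as speeding recovery.

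**Working it through.** **Massage duration.** From Table 1: two thighs × (60 + 60 + 60 s) + trunk (120 + 120 + 120 s) = 360 + 360 = 720 s = 12 min. This reproduces the stated duration.

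**Offsets from the end of stress.** I3: 0 min. I4: 12 min. I5: 60 + 12 = 72 min. The differences are 12 min (I4–I3), 72 min (I5–I3) and 72 − 12 = 60 min (I5–I4). These are minimums, since transfer and repositioning are not counted.

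**Same label, minutes since end of stress.**

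| Moment | I3 | I4 | I5 |
|---|---|---|---|
| R2 | 0–5 | 12–17 | 72–77 |
| R4 | 10–15 | 22–27 | 82–87 |
| R6 | 30–35 | 42–47 | 102–107 |
| R9 | 60–65 | 72–77 | 132–137 |
| R12 | 115–120 | 127–132 | 187–192 |

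I3 ends at 120 min, so I5 from R8 (122–127 min) onward and I4 at R12 have no stress-only counterpart.

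**Testing the other reading.** Suppose the moments ran from the end of stress in every session. In I5 the massage occupies 60–72 min, so R9 (60–65) would fall inside it and R10 (70–75) would straddle its end. R12 would end 120 − 72 = 48 min after massage, against the stated 2 h. That reading does not fit the text.

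**Size with zero massage effect.** This is an illustration. Assume the fraction of the initial HRV deficit remaining is D = exp(−(m + o)/τ), with m the window midpoint and o the offset, both in minutes. If a fraction p has recovered at 60 min, τ = −60/ln(1 − p). The protocol takes recovery to be reached at 60 min; p = 0.95 gives τ = 20.0 min. At R2, m = 2.5:

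- I3: exp(−2.5/20.0) = 88.3%
- I4: exp(−14.5/20.0) = 48.5%
- I5: exp(−74.5/20.0) = 2.4%

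| Moment | Deficit I3 / I4 / I5 (%) | Spurious gap I4–I3 / I5–I3 / I5–I4 (points) |
|---|---|---|
| R2 | 88.3 / 48.5 / 2.4 | 39.8 / 85.8 / 46.1 |
| R4 | 53.6 / 29.4 / 1.5 | 24.1 / 52.1 / 28.0 |
| R6 | 19.7 / 10.8 / 0.5 | 8.9 / 19.2 / 10.3 |
| R9 | 4.4 / 2.4 / 0.1 | 2.0 / 4.3 / 2.3 |
| R12 | 0.3 / 0.2 / 0.0 | 0.1 / 0.3 / 0.1 |

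On this curve the time to 95% recovery, read on each session's own clock, would be 60 min in I3, 60 − 12 = 48 min in I4 and 0 min in I5.

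**Range.**

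| Assumption | R2 deficit I3 / I4 / I5 (%) | Largest gap at R12 (points) |
|---|---|---|
| p = 0.90 (τ = 26.1) | 90.9 / 57.3 / 5.7 | 1.0 |
| p = 0.99 (τ = 13.0) | 82.5 / 32.9 / 0.3 | 0.0 |
| τ = 40 | 94 / 70 / 16 | 5.3 − 0.9 = 4.4 |

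The last row implies only 1 − exp(−60/40) = 78% recovery at 60 min. That is slower than the protocol's own premise, so it serves as a sensitivity case.

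**The case against.** Much of the case on the other side stands, and it limits the point.

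- **Minute zero is inferred.** The Primary outcome section never defines it. Counting from the end of massage is the reading that fits the other sections, and Figures 1 and 3, which are not shown, may add timing detail.
- **Late windows are nearly clean.** The Abstract describes the primary outcome as HRV measured 2 h after each intervention. Taken literally, that is where the bias almost vanishes. But the Primary outcome and Statistical analysis sections use all of R2–R12, and bringing recovery forward is an early-window question.
- **The 60-min premise is checked.** A reader might infer that recovery by 60 min is never tested. It is: in this cross-over, R8 and R9 against R1 in I3 test it in the same participants, though not within the I5 session.
- **HRV in the I5 pre-massage hour.** A reader might infer that none is recorded. The text lists only cardiorespiratory readings for that hour, but the figures may include HRV, so its absence cannot be asserted.
- **Enhanced recovery is not wholly an artefact.** If HRV returns towards baseline and stops there, elapsed time cannot push I5 above its own R1. I5 against I2 (massage alone) is also aligned on time since massage. And if I3 has reached a plateau, the missing control after 120 min matters less; that would have to be assumed.
- **A common clock is not a full cure for I5–I4.** At 75–80 min after stress, I4 is 63–68 min past its massage and I5 only 3–8 min. A short-lived massage effect would then favour I5. No single clock isolates timing.

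**Conclusion.** The point holds for comparisons of I3, I4 and I5 at the same R label. As the text stands, these confound massage with 12 min (I4–I3), 72 min (I5–I3) or 60 min (I5–I4) of extra natural recovery, and the stated adjustment does not correct it. The offsets follow directly from the article. The size of the bias rests on an assumed recovery curve and cannot be put in milliseconds. With recovery 90–99% complete at 60 min and no massage effect, the spurious gap at R2 is 34–50 points of the initial deficit for I4–I3, 82–86 for I5–I3 and 33–52 for I5–I4. It falls to 1 point or less at R12, or about 4 points with τ = 40 min.

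The documents do not support saying that every window is seriously biased or that the question of enhanced recovery is unanswerable. The damage is to the early and middle windows. Separately, I5 beyond 120 min after stress has no stress-only control.

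**What to change.** 1. State minute zero of the R-moments for each intervention.
2. For I4–I3 and I5–I3, define windows by minutes since the end of stress, cut from the RR recording.
   - I4–I3: common windows from 20–25 to 115–120 min (8–13 to 103–108 min after the I4 massage).
   - I5–I3: 75–80, 90–95 and 115–120 min (3–8, 18–23 and 43–48 min after the I5 massage).
3. Apply the same indexing to the cardiorespiratory measures.
4. For I5–I4, either use the common post-stress clock and state that time since massage differs by 60 min, or compare each with its time-matched I3 window.
5. Report I5 beyond 120 min after stress as uncontrolled, or extend I3 recording by 72 min to 192 min.
6. If the schedule figures do not already include it, keep RR recording running through the I5 pre-massage hour and use 55–60 min as the within-session reference.

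**Cost.** This is mostly re-cutting recordings. It assumes that RR is recorded continuously and stored, which the article implies but does not state; 75–80 min is not a listed moment. Step 6 adds only recording time. The main downside is that the controlled I5–I3 comparison covers just 120 − 72 = 48 min after massage unless I3 is extended. None of this changes the interventions.

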However, in the study of Arroyo-Morales et al. [15] some gaps can be identified in the literature. Before the massage technique, the participants performed 15 min of active and passive recovery, the massage technique had five different modalities of tissue manipulation applied in regions that were not protagonists during the stress, with prolonged duration and applied only at one moment. These details in the design of the study may influence the responses found in the recovery of autonomic modulation of heart rate, especially considering practical applications. However, the main gap addressed by the present study protocol is related to the moment of application of massage as a recuperative technique. To study the optimal timing of the technique seems interesting since various sports modalities participate in several competitions throughout the day and, thus, it is necessary to understand the best moment of application of the recuperative technique to guarantee the best performance of the athletes.

The recovery of autonomic modulation of heart rate has been considered an important global marker of athlete recovery. Ihsan et al. [16] reported that the return of HRV values is a good indicator for exercise dynamics to be applied in training or in competitions. In addition, although massage is widely used as a recuperative technique, there are gaps in the literature regarding the effectiveness of massage in the autonomic modulation of heart rate and cardiorespiratory parameters; and especially in relation to the best moment of application. It is unclear whether performance of the massage technique has a beneficial effect on HRV both to anticipate its recovery and potentiate the effects of recovery depending on the moment of its application.

The present study is a randomized clinical trial aimed at investigating the effects of massage as a recuperative technique on the recovery of autonomic modulation of heart rate and cardiorespiratory parameters in physically active young people comparing two distinct scenarios: (1) immediately after stress in order to investigate if the technique anticipates the recovery of the ANS, and (2) immediately after the recovery moment of the ANS in order to investigate whether the technique potentiates the recovery of the ANS.

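### I5 is meant to test massage on a recovered ANS, but the text states no HRV window between stress and massage, so potentiation can be separated from continuing recovery only in part, through I3

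*Protocol article*

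**What the plan says.** The second scenario in the Background places the massage "immediately after the recovery moment of the ANS in order to investigate whether the technique potentiates the recovery of the ANS". The section on study interventions turns this into a fixed clock time. It says that "the massage technique will be applied at the exact moment of ANS recovery", a moment taken from an earlier investigation with the same stress protocol, and then that "at I5 the massage will be applied 60 min after the end of the stress protocol".

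For HRV in I5, that section gives two occasions. First, "the HRV behavior of the participant will be evaluated before the stress protocol, and the massage technique will be applied"; then, after the massage, "posteriorly there will be follow up for 2 h in order to see if there is potentiation of HRV recovery". The stress protocol section agrees: it describes the 2 h of RR capture as following the massage.

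The primary outcome section lists the HRV windows, beginning "R1 (initial 5 min of rest before performing the interventions), R2 (initial 5 min of recovery" and ending with R12 at 115-120 min. It assigns none to the hour between stress and massage in I5.

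The secondary outcomes section does deal with that hour: "in I5 these variables will be collected 1 h prior to the application of the massage at minutes 1, 3, 5, 7, 10" and onward to minute 60. The variables meant are blood pressure, heart rate, respiratory rate and oxygen saturation.

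The statistical analysis compares the five interventions and the moments R1 against R2-R12, with adjustment for the baseline value of each variable.

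**The concern.** Potentiation, as the protocol uses the word, means an effect of massage on a system that has already recovered. To show it, one needs to know the HRV state when the massage begins. In I5 the only stated HRV reference within the session is R1, taken before stress.

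That leaves two ways to misread a result. If a man is still below R1 at 60 min, a later rise may be ordinary recovery. If he is already above R1 at 60 min, that excess may be credited to the massage.

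The second objective and the conclusion about the best moment of application both depend on telling these cases apart. Calling the imported time exact suggests a verification that the text does not describe for I5.

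**Working it through.** The plan has no calculated figure on this point. The check compares what is measured in each session and puts the windows on one clock.

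**What is measured between the end of stress and 60 min**

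| Session | HRV windows stated in the text | Cardiorespiratory variables |
|---|---|---|
| I3 (stress only) | R2-R8 (0-5 to 50-55 min), then R9 at 60-65 min | minutes 1 to 60 |
| I5 (stress, massage at 60 min) | none | minutes 1 to 60 |

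**Which clock I5 uses.** The interventions and stress protocol sections place the 2 h follow-up after the massage. The secondary outcomes section treats the hour before the I5 massage as additional to the 2 h of recovery. The recovery clock in I5 therefore starts after the massage. If it started at the end of stress, R12 would close at 120 min, only 120 - 72 = 48 min after the massage ended, which contradicts the stated 2 h.

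**Offset.** Delay to massage is 60 min (study interventions) and massage duration is 12 min (massage protocol). Offset = 60 + 12 = 72 min, assuming no delay between steps. Minutes since stress for an I5 window = nominal minutes + 72. In I3, nominal minutes are already minutes since stress.

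| Window | I3, min since stress | I5, min since stress | I3 window overlapping the I5 window |
|---|---|---|---|
| R2 | 0-5 | 72-77 | R10 (70-75), 3 min shared |
| R3 | 5-10 | 77-82 | none |
| R4 | 10-15 | 82-87 | none |
| R5 | 20-25 | 92-97 | R11 (90-95), 3 min shared |
| R6 | 30-35 | 102-107 | none |
| R7 | 40-45 | 112-117 | R12 (115-120), 2 min shared |
| R8 | 50-55 | 122-127 | beyond the end of I3 |
| R9 | 60-65 | 132-137 | beyond the end of I3 |
| R10 | 70-75 | 142-147 | beyond the end of I3 |
| R11 | 90-95 | 162-167 | beyond the end of I3 |
| R12 | 115-120 | 187-192 | beyond the end of I3 |

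Three of the 11 I5 follow-up windows overlap an I3 window, and each only partly. Three more (R3, R4, R6) fall inside the I3 follow-up but between its windows. Five (R8-R12) have no stress-only counterpart. A comparison by label sets each I5 window against an I3 window 72 min earlier after stress, so a higher I5 value would be expected from elapsed time alone while recovery is still going on.

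**How many men might not have recovered at 60 min (illustration only).** The documents give no spread of recovery times, so these inputs are assumed.
- Normal, mean 45 min, SD 15: z = (60 - 45)/15 = 1.00, 16% beyond 60 min, 0.16 × 40 ≈ 6 men.
- Normal, mean 45 min, SD 20: z = (60 - 45)/20 = 0.75, 23%, 0.23 × 40 ≈ 9 men.
- Median of 60 min: 50%, 20 men.

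**The case against.** The best defence is I3. This is a cross-over in which every man does all five interventions. I3 applies the same stress without massage and records HRV at 50-55 and 60-65 min, and the protocol gives I1-I3 the role of establishing reference behaviour. Recovery near 60 min is thus observed in the same men, and unfinished recovery is present in I3 as well as I5. A contrast of I5 with I3 at equal time since stress removes it without needing a pre-massage value. This stands up to about 120 min after stress. It does not show a man's state in the I5 session, which is a different visit, and the analysis section does not describe matching on time since stress.

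A second defence is that the gap is partly silence. The sentence listing cardiorespiratory variables sits under secondary outcomes, where HRV would not be expected, and Fig. 1, whose legend has an HRV symbol, is not available here. This also stands: the finding is that the text states no such window, not that none exists. Yet the interventions section describes the I5 HRV assessments directly and mentions none in that hour.

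Third, the shares of unrecovered men follow only from the assumed inputs. That is correct, and the conclusion does not depend on them.

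**Conclusion.** The point holds in limited form. The text states no HRV measurement between stress and massage in I5, so the recovered state that defines potentiation is imported from an earlier study and not verified in that session. Within I5, potentiation cannot be separated from continuing recovery. Through I3 it can be separated in part: three partly overlapping windows as scheduled, nothing after 120 min, and only if the analysis matches on time since stress, which the plan does not say.

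A reader might infer more: that no HRV precedes the massage, that the 60-min premise is never checked in these men, or that the two explanations cannot be told apart at all. The documents do not support this. R1 precedes both stress and massage, and I3 provides both an indirect check near 60 min and a comparator to about 120 min. Nor do they support any particular number of unrecovered men.

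The conclusion assumes that I5 recovery is counted from the end of massage, that steps follow without delay, and that Fig. 1 does not already mark HRV in that hour. The change is worth making because it serves the trial's main question at little cost.

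**What to change.** Leave the massage timing as it is and change the measurement and the contrast.

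1. Store RR intervals during the I5 pre-massage hour with the V800, which already supplies heart rate then. Extract HRV at the I3 post-stress windows R2-R8, plus one window at 55-60 min. Extract 55-60 min in I3 too, since its present windows there are 50-55 and 60-65.
2. Define potentiation as the change from the 55-60 min window in I5 against the same man's change in I3 over the same minutes since stress, limited to about 120 min. One way is to cut the I3 recording at the minutes of I5 R2-R7 (72-117), if it is stored continuously.
3. Report descriptively how many men were back at their resting level before massage. Do not repeat the contrast in those men only: selecting on a noisy I5 value with no matching selection in I3 invites regression to the mean.
4. Describe the timing as 60 min after the end of stress, and drop the claim that "the massage technique will be applied at the exact moment of ANS recovery".
5. If Fig. 1 already marks HRV in that hour, say so in the interventions and primary outcome sections and use it in the analysis.

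The cost is a few extra analysis windows in I5 and I3, one more hour of stored RR data, and a wording change. No extra visit is needed.
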